##### Secondary outcomes

Secondary outcomes comprise all other domains of the EPIC-26 with the according MID changes (sexual function, MID ≥ 10; irritative/obstructive symptoms, MID ≥ 7; gastrointestinal symptoms, MID ≥ 5; vitality/hormonal function, MID ≥ 4), changes in health-related quality of life according to the EQ-5D-5L, changes in depression and generalized anxiety according to the PHQ-4 as well as in changes to patient enablement according to the PEI.

### Interim analyzes {21b}

The study is scheduled to run for 36 months. Flanked by a 12-month pre-study and an 8-month follow-up, data collection will take place over a period of 28 months. This ensures that the required calculated number of cases can be safely achieved. A first interim analysis will be performed in a group sequential design with Haybittle-Peto barriers with interim analysis after 24 weeks, in order to make adaptations concerning the duration, the number of cases, and the design elements. Specifically, the treatment discontinuation (insufficient adherence) and the adequacy of the data collection forms will be evaluated in order to possibly adapt the study process.

### Methods for additional analyses (e.g., subgroup analyses) {20b}

#### Process evaluation

According to the Medical Research Council Guidance on the development and evaluation of complex interventions [42], a feasibility analysis, an impact analysis, and an investigation of change processes, as well as an analysis of the implementation quality will be carried out in the corresponding project phases as part of a process evaluation. A qualitative process evaluation in three modules will be performed. The three modules are: feasibility, impact, and implementation. The evaluation will be done by semi-structured interviews with patients (and relatives), urologists, psycho-oncologists, and study nurses. Patients from the intervention group and the control group are interviewed at two time points (approximately 12 weeks and approximately 52 weeks after surgery). The data are qualitatively analyzed using content analytic methods. Criteria for Module 1 are based on the feasibility criteria [43], for assessing the acceptance and feasibility of the intervention and study procedures. Analysis of implementation factors in Module 3 follows the Consolidated Framework for Advancing Implementation Science (CFIR) [44].

Thus, the results of the effectiveness study can be explained and the effective components of the intervention can be described. In the context of later implementation and dissemination, the benefit of the intervention—adapted on the basis of the program theory—can be further increased.

### Methods in analysis to handle protocol non-adherence and any statistical methods to handle missing data {20c}

The influence of missing values will be analyzed in sensitivity analyses (multiple imputation). To analyze the secondary outcome variables, mixed linear models for repeated measures will be used, analogous to the analysis of the primary endpoint. These analyses will be performed without controlling for multiple experimental errors.

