### Criteria for discontinuing or modifying allocated interventions {11b}

No primary radical prostatectomy performedChange of center to a prostate cancer center not participating in the studyPatient requestPatient is no longer able to participateIncreased psychological stress induced by the ePROM survey (clarification of causes in the consultation), which cannot be alleviated despite consultations and further measures

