### Sample size {14}

Based on the information that preoperative urinary continence issues are observed in 3% [35] and a continence rate of 20% (0 pad/day) is anticipated 6 weeks postoperatively [7], the required sample size is calculated as follows: A total of 672 patients who undergo prostatectomy at participating centers will be considered for inclusion in the study. Of these, 412 are expected to be excluded for the following reasons: 336 patients (50%) will not provide informed consent, 10 patients (3%) will have preoperative urinary incontinence, and 66 patients (20%) will show no urinary incontinence 6 weeks postoperatively. The remaining 260 patients will be randomized, with 130 assigned to the intervention group and 130 to the control group. Data analysis will be conducted for 104 patients in each group, with 26 patients (20%) anticipated to be excluded from analysis due to dropout (see Fig. 4).

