**Fig. 4 Fig4:**
[figure not shown]
Consort data flow

To detect a mean effect size of 0.4 (Cohen’s *d*) for the primary endpoint, 99 patients per group are required, assuming 80% power and a 5% two-sided error.

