## Statistical methods

### Statistical methods for primary and secondary outcomes {20a}

#### Summative evaluation

##### Primary outcome

To calculate the primary endpoint, the difference is calculated between the scores on the urinary incontinence scale of the EPIC-26 at 52 and 6 weeks postoperatively. Changes regarding urinary incontinence (minimally important difference (MID) ≥ 9) at 52 weeks postoperatively compared with 6 weeks postoperatively are considered. The primary endpoint will be examined in an intention-to-treat analysis. The comparison regarding the superiority of the primary endpoint will be performed by using a mixed linear model for repeated measures. The variables included in the model comprise intervention/control group, time, group*time, center, tumor stage, and age group.

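### The named missing-data check, multiple imputation, has no stated missingness assumption; in its standard form it shares the primary model's missing-at-random assumption and would not test informative dropout

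*Protocol article*

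**What the plan says.** The section on protocol non-adherence and missing data {20c} gives one sentence to the problem: "The influence of missing values will be analyzed in sensitivity analyses (multiple imputation". It names no imputation model, auxiliary variables or missingness assumption. It mentions no not-at-random analysis, but it excludes none.

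For the primary outcome, Statistical methods {20a} says "The primary endpoint will be examined in an intention-to-treat analysis" and "The comparison regarding the superiority of the primary endpoint will be performed by using a mixed linear model for repeated measures". The model contains group, time, their interaction, center, tumor stage and age group.

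Sample size {14} plans for loss: "The remaining 260 patients will be randomized, with 130 assigned to the intervention group and 130 to the control group", then "Data analysis will be conducted for 104 patients in each group", "with 26 patients (20%) anticipated to be excluded from analysis due to dropout".

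Three features bear on why patients might leave:
- The control arm is surveyed after surgery at weeks 6, 24 and 52 {6b}, the intervention arm at weeks 6, 12, 18, 24, 36 and 52 {11a}. Only the intervention arm receives alert-triggered contact.
- The trial is open label and the outcome is patient-reported {17a}.
- The discontinuation criteria {11b} include "psychological stress induced by the ePROM survey", where it cannot be relieved.

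**The concern.** The purpose stated in {20c} is to learn how much missing values influence the result. That requires varying the assumption on which the primary result depends. A likelihood-based mixed model depends on MAR: given the observed data, patients who leave would have scored as comparable patients who stay. Standard multiple imputation from the same variables makes the same assumption and gives nearly the same estimate. A reader who saw the two agree could take this as robustness when the assumption at risk had not been varied.

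Informative dropout is plausible in this design. One arm is asked twice as often and is contacted when scores cross thresholds, and both arms know their allocation. Patients could leave week 52 unanswered for reasons linked to their continence, and those reasons could differ by arm.

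**Working it through.** **Inputs from the article.** 130 randomized and 104 analysed per arm; dropout 26/130 = 0.20; d = 0.4, 80% power, two-sided 5%, 99 required per group (Sample size {14}); MID 9 points (Outcomes {12}).

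**Inputs that are assumptions.** The shift δ, by which intervention-arm dropouts lie below their MAR prediction, and the SD in points. The article gives neither.

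**1. The plan's own figure.** n = 2(1.96 + 0.8416)²/0.4² = 98.1, rounded up to 99 per group. This reproduces the stated number. Power with 104 per arm is about 82%. The sample size is not in dispute.

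**2. Significance limit.** SE = √(2/104) = 0.139 SD, and 1.96 × SE = 0.272 SD. The SE is held fixed below; covariate adjustment would change it.

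**3. Tipping point for a shift in one arm.** Effect over all randomized patients = MAR estimate − 0.20 × δ. Significance is lost at δ = (d − 0.272)/0.20, and the effect reaches zero at δ = d/0.20.

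| Observed d | δ that loses significance | δ that gives zero effect |
|---|---|---|
| 0.30 | 0.14 SD | 1.5 SD |
| 0.40 | 0.64 SD | 2.0 SD |
| 0.50 | 1.14 SD | 2.5 SD |

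**4. In points, for a range of assumed SDs.**

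| Assumed SD | 0.64 SD | 0.14 SD | Effect left from d = 0.40 if dropouts are 9 points low |
|---|---|---|---|
| 15 | 9.6 | 2.1 | 0.40 − 0.20 × 0.60 = 0.28 |
| 22.5 | 14.4 | 3.2 | 0.40 − 0.20 × 0.40 = 0.32 |
| 30 | 19.2 | 4.2 | 0.40 − 0.20 × 0.30 = 0.34 |

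At d = 0.40, a deficit of one full MID in every intervention-arm dropout leaves the effect above 0.272 at each SD. From d = 0.30 the same deficit leaves 0.18, 0.22 and 0.24, all below it.

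**5. Error rate with no true effect.** The spurious effect is 0.20 × δ. At δ = 0.5 SD it is 0.10, and the rejection probability is 1 − Φ(1.96 − 0.10/0.139) + Φ(−1.96 − 0.10/0.139) = 11%. At 0.25 SD it is 6.5%, and at 1.0 SD it is 30%, against a nominal 5%.

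**6. Does standard multiple imputation reveal this?** A simulation used 130 per arm, three visits, assumed correlations of 0.5 to 0.6, 20% missing at week 52, 1,500 replicates and 20 imputations. A regression-based MAR estimate stood in for the mixed model, and imputation used the same variables.

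| δ in intervention-arm dropouts | True effect | MAR estimate | Standard imputation | Delta-adjusted imputation |
|---|---|---|---|---|
| 0 | 0.399 | 0.401 | 0.401 | 0.401 |
| 0.5 SD | 0.303 | 0.404 | 0.404 | 0.305 |
| 1.0 SD | 0.204 | 0.402 | 0.402 | 0.202 |

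Standard imputation repeats the MAR estimate and does not show the bias. Delta adjustment recovers the truth here because the simulation supplies the true δ. In the trial δ is unknown, so a range must be reported.

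**The case against.** The strongest objection is that {20c} does not say that the imputation is under MAR. Multiple imputation can carry delta or reference-based shifts, the sentence speaks of analyses in the plural, and such detail commonly sits in the SAP or full protocol, which are not shown. This stands as a limit. A reader might infer that the plan has only an MAR check and cannot detect any influence of dropout, but the documents do not support that. The point is conditional: the named method does not serve its stated purpose unless not-at-random scenarios are part of it.

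Second, imputation need not duplicate the mixed model. PHQ-4, EQ-5D-5L and the other EPIC-26 domains are collected but are not in the primary model. If distress drives dropout, imputation that uses PHQ-4 would address part of that mechanism. This also stands, but such an analysis makes MAR more credible and does not test departures from it.

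Third, Sample size {14} speaks of excluding 26 patients per arm from analysis. If the primary analysis really did so, imputation over all 130 would be a different analysis that uses partial data. It would still be an MAR analysis, and the article elsewhere commits to intention-to-treat.

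Fourth, a reader might infer from the survey-stress criterion that dropout will be informative and heavier in the intervention arm. The documents do not show this. Section {11b} governs stopping or modifying the intervention, which is not the same as losing the week-52 score. It applies only where the stress cannot be relieved, and no rate is given. The planned 20% is equal by arm, and reminders and closer nurse follow-up could push the imbalance the other way.

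**Conclusion.** The point holds in conditional form. Multiple imputation is the one sensitivity method that the article names for missing data, and its assumption is not stated. In standard form it would not test the assumption on which the primary model rests. The primary analysis itself is not faulted.

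The size depends on the observed effect. At d = 0.40 the result is fairly sturdy: a shift of about 0.64 SD in one arm would be needed. At d = 0.30, still nominally significant, about 0.14 SD would be enough. These figures assume 20% missing in the intervention arm, a shift in that arm only, and the SE for 104 per arm. The values in points also need an SD that the article does not give. The shifts are scenarios, not predictions.

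**What to change.** 1. State the missingness assumption of the multiple imputation. Keep an MAR version that includes auxiliary variables such as PHQ-4 and EQ-5D-5L.
2. Add a delta-adjusted tipping-point analysis of the week-52 EPIC-26 incontinence score. Vary the shift separately in each arm, in steps tied to the 9-point MID, and report the combinations at which the conclusion changes.
3. Control-based imputation for intervention-arm dropouts is an optional addition.

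Restricting the imputation model to weeks 6, 24 and 52 is not recommended as a requirement. It would give both arms the same visits, but it discards the week 12, 18 and 36 scores, which are informative about intervention-arm dropouts. That is a trade-off.

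The shifts should be fixed before outcomes by arm are seen, because the analysts are not blinded {17a}. The cost is extra programming and one more table, with no new patients or data.

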### Plans to give access to the full protocol, participant-level data and statistical code {31c}

The full study protocol is available from the corresponding author. The participants in this study do not provide explicit consent for public data sharing. To protect their privacy, the data will not be available for public access. The data are available upon reasonable request, provided that the request is for research purposes, the confidentiality of the data is maintained, and appropriate ethical approval is demonstrated. Statistical code will be available from the IMSB, Cologne, Germany, upon reasonable request.

### Oversight and monitoring

#### Composition of the coordinating center and trial steering committee {5d}

The Steering Board is composed of the project managers of the sub-projects. Each partner is represented by at least one member of the Steering Board. The Steering Board advises and decides on matters of general or fundamental importance within the consortium. The Steering Board is advised by a patient representative from the Federal Association of Prostate Cancer Self-Help (Bundesverband Prostatakrebsselbsthilfe e.V.). The role of the patient representative is to bring in the patient perspective, ensure that the needs and concerns of patients are considered, and advocate for patient-centered approaches throughout the study. The tasks of the Steering Board members include in particular:Supervision of the implementation of the plans and objectives in the project,Monitoring the progress and development of the partners. This includes, in particular, compliance with the milestones specified in the joint application to the funding organization,Reviewing and commenting on planned publication projects, as well as counseling and arbitration in the event of disagreements, e.g., with regard to the naming and order of authors,Arbitration in the event of disagreements regarding the use of data from the project, andDecisions on the inclusion or exclusion of partners.

The project group is made up of the local study coordinators of the partners, along with a patient representative from the Federal Association of Prostate Cancer Self-Help (Bundesverband Prostatakrebsselbsthilfe e.V.). The project group meets once a month to discuss the progress and problems of the project.

The study nurse group is made up of the study nurses from all recruiting centers and the study coordinators from the consortium management and meets weekly to discuss practical problems in the study process.

### Composition of the data monitoring committee, its role and reporting structure {21a}

A DMC is not planned as part of the study, as only standard care is being compared to enhanced follow-up care—serious adverse events (SAEs) are therefore not expected. Regular monitoring of the data and reporting to all partners is carried out by OnkoZert (Neu-Ulm, Germany) after the start of recruitment. The content of the reporting will be discussed at the project group meetings and steering board meetings. Independent patient representatives are also part of the project group and the steering board in an advisory capacity.

### Adverse event reporting and harms {22}

In this study, we have developed a comprehensive plan for collecting, assessing, reporting, and managing both solicited and spontaneously reported adverse events (AEs) and any unintended effects related to the trial interventions or conduct. While the primary comparison involves enhanced follow-up care versus standard post-prostatectomy care, potential AEs such as increased psychological strain due to repeated questioning or the focus on the illness have been considered. To mitigate this, any participant reporting psychological distress will be offered a medical consultation. Additionally, technical issues during the survey process may also lead to participant frustration or stress, which has been identified as another potential AE. In such cases, participants are encouraged to contact the study nurses or study coordination team to report these issues and receive prompt assistance. All participants are provided with contact information for the study leadership, coordination team, and Study Nurses at their center, allowing them to report any AEs or concerns as they arise. The study nurses are in continuous communication with the study coordination team, which is available at all times for immediate support. To ensure ongoing monitoring and management of AEs, weekly study nurse joint meetings (JF) are held to review patient feedback and monthly project group meetings are used to discuss all reported AEs, as well as qualitative feedback from participants. If necessary, protocol adjustments are made based on these discussions. All AEs will be documented in the study database, in a free-text field labeled “Special Considerations,” to ensure comprehensive tracking, evaluation, and management of any adverse effects associated with the study interventions or its conduct. This approach ensures that potential harms are promptly addressed, while participant safety and well-being are maintained throughout the study.

### Frequency and plans for auditing trial conduct {23}

Audits are planned once a year after the start of recruitment and are organized by the consortium management.

### Plans for communicating important protocol amendments to relevant parties (e.g. trial participants, ethical committees) {25}

Relevant changes to the study protocol are submitted by both the consortium management and all participating centers to the respective ethics committees for approval.

### Dissemination plans {31a}

The study entry in the ClinicalTrials.gov registry is continuously updated. Information about the PRO-P project can be found on the project website https:\\pro-p.info. It is planned to continuously update the website and present study-related events as well as layperson-friendly study results on the website. At the conclusion of the study, a kickoff meeting is planned, to which both healthcare providers as well as patients, and patient representatives will be invited. The preliminary study results will be presented and discussed during this meeting. Study results are presented at scientific conferences and preferably published open-access Table 

## Discussion

This is the first multicenter randomized controlled study investigating the effectiveness of postoperative electronic patient-reported outcome measures (ePROMs) following surgical intervention (radical prostatectomy for localized prostate cancer). We anticipate a significant reduction in the physical symptom burden, primarily urinary incontinence, and psychological symptom burden in the intervention group, accompanied by improvements in patient competence and health-related quality of life.

The process evaluation based on the perspectives of both patients and healthcare providers is expected to provide insights into facilitating factors as well as barriers in the implementation, execution, and adoption of ePROMs in this context.

The structured follow-up care within the framework of the PRO-P study closes a gap in care in the follow-up and treatment of physical and psychological consequences of radical prostatectomy.

The implementation of new digital applications remains a challenge, taking into account the interfaces with different hospital information systems at the prostate cancer centers. At all centers, however, there is already corresponding preparatory work through the PCO study, so only the additional digital survey tools need to be implemented. Another obstacle could be the unwillingness of patients to participate in the electronic collection of data, because of a lack of technical means, low digital health literacy, and/or objections to digital data collection. Language barriers among patients could possibly lead to a lack of willingness to participate. This has already been taken into account when calculating the number of cases. However, older patients nowadays widely use smartphones or desktop computers. Furthermore, study nurses at the prostate cancer treatment centers can provide additional assistance.

### Utilization potential

The relevance for the health care system lies in early detection, counseling, and treatment of distressing postoperative symptoms and improved cross-provider networking between centers and office-based urologists. In the future, follow-up care using ePROMs could be integrated into the legally required electronic patient record. In the long term, electronic follow-up care by means of ePROMs can and should be led and managed by outpatient urology practices.

EHealth interventions may clarify problems and thus resources could be saved. Extrapolation to other areas of health care is possible. Various publications address the inclusion of PROMs in the oncological follow-up of patients with different tumor types [24].

## Conclusion

In light of existing efficacy indications for breast cancer, colorectal cancer, and advanced malignancies, this study represents a pioneering investigation into symptom monitoring for prostate cancer, particularly in the context of primary surgical intervention (radical prostatectomy). Anticipated outcomes include a reduced symptom burden and improved quality of life for prostate cancer patients. Expectations encompass gaining valuable insights into the intervention's mechanism of action, its further refinement, and elucidation of inhibitory and facilitative factors influencing the implementation of the intervention.

## Trial status

Study protocol version 2.3, dated May 10, 2023. Recruitment started on April 01, 2023. The end of recruitment is planned for July 31, 2024. The end of data collection/last visit is planned for August 31, 2025. The first results are expected in December 2025*.*

Due to the complexity of the technical infrastructure and the corresponding need for ongoing coordination with the data protection institutions, an extended technical development period and repeated adjustments to the study protocol were necessary, meaning that recruitment could only start later than originally planned. Another consequence was that the study protocol could only be submitted late in the recruitment process.

